### Study hypothesis and objective(s) in the phase II part

1.3

Hypothesis:

The addition of rosuvastatin to NACTRT will improve the pCR rate by 10% (from 15% to 25%).

Primary objective:

To determine the impact of rosuvastatin in improving pCR in patients with locally advanced rectal cancer undergoing NACTRT.

Secondary objectives:

To compare the frequency and severity of adverse events in the two arms.To compare post-operative morbidity and mortality in the two arms.To identify other potential prognostic and predictive factors determining outcomes.To compare the DFS in the two arms.To compare the OS in the two arms.Evaluate expression and localization of SATB1 and SATB2 across paired human colon/rectum and tumor samples.Correlation of expression of SATB1 and SATB2 across different grades and stages of tumor samples towards understanding CRC progression.Understand the role of SATB proteins in tumor regeneration and disease relapse by validation of the association of its expression across differentiated and undifferentiated tumors.Correlation of expression of SATB proteins across colorectal cancer subtypes-classical adenocarcinoma, mucinous adenocarcinoma, and signet ring pathology tumors.

If the phase 2 study has positive results, we plan to proceed to a phase 3 study.

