#### End of study visit

2.3.7

Patients will receive rosuvastatin for 12–16 weeks, with the treatment being discontinued 1 day prior to surgery for operable patients. The final study visit for these patients will coincide with their MDTB appointment, where the final surgical histopathology report (approximately 10–14 days post-surgery) will be reviewed. For patients deemed inoperable, the study will conclude on the day the decision of inoperability is made. At this visit, a final safety follow-up and pill count will be conducted. Following this, there will be no further active intervention, and patients will be monitored for survival. No protocol-mandated imaging or re-evaluation is planned; patients will be followed according to standard surveillance guidelines for rectal cancer patients who have undergone multimodality treatment.

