### Statistical consideration

2.5

A) The primary efficacy variable is a pathological complete response which is defined as the absence of microscopic tumors in the resected specimens in patients who undergo surgery following neoadjuvant chemoradiotherapy.

B) The secondary efficacy variables are toxicity and 3-year DFS.

C) Toxicity will be assessed as detailed below. The NCI Common Terminology Criteria for Adverse Events version 4 (NCI CTCAE v4.03) will be used to classify and grade the intensity of adverse events during and after chemo-radiotherapy. The worst grade of each toxicity episode will be recorded. All events regardless of attribution will be graded so as to ensure objectivity in reporting as per accepted international guidelines. The details will be entered in the dataset.

D) Any adverse event that occurs from the day of randomization until the end of study visit will be defined as an acute adverse event. Events that occur thereafter will be defined as chronic adverse events. Both acute and chronic adverse events will be recorded however only events happening till 30 days after surgery will be reported and not beyond.

E) Postoperative morbidity and mortality will be any event occurring from the day of surgery until 30 days.

F) Disease-free survival is defined as the time from the date of randomization until the date of disease recurrence or until death from any cause.

G) Progression-free survival (PFS) is defined as the time from the date of randomization until the date of disease recurrence or until death from any cause. If there is a clinical suspicion of progression, further workup and management will be as per the institutional standard. Progression will be assessed by the investigator using appropriate workup and investigations, as per routine care.

H) Overall survival is defined as the time from the date of randomization until the date of death from any cause.

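### The acute/chronic adverse-event cut falls about 10–14 days after surgery in operated patients, so the acute class mixes treatment and surgical events and the reported chronic class spans only 16–20 postoperative days

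*Protocol article*

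**What the plan says.** All references are to the protocol article.

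- **Acute class (2.5 D):** "Any adverse event that occurs from the day of randomization until the end of study visit will be defined as an acute adverse event".
- **Chronic class (2.5 D):** "Events that occur thereafter will be defined as chronic adverse events". Both classes are recorded, but "only events happening till 30 days after surgery will be reported and not beyond".
- **Where the final visit falls (2.3.7):** for operated patients it "will coincide with their MDTB appointment, where the final surgical histopathology report (approximately 10–14 days post-surgery) will be reviewed". For the others: "For patients deemed inoperable, the study will conclude on the day the decision of inoperability is made".
- **Postoperative outcome (2.5 E):** "Postoperative morbidity and mortality will be any event occurring from the day of surgery until 30 days".
- **Objectives (1.3):** the frequency and severity of adverse events is one between-arm comparison. Another is "To compare post-operative morbidity and mortality in the two arms".
- **Attribution (2.5 C, 2.3.10):** events are graded and recorded whatever their cause.
- **Second reporting limit (2.3.10):** adverse events after the study period has ended are not reported.

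**The concern.** The words acute and chronic suggest early treatment toxicity and late toxicity. The dates behind them do not match that meaning. In an operated patient the boundary is an appointment in the second week after surgery. The acute class therefore holds everything from the start of NACTRT through the operation and early recovery. The chronic class, as reported, holds the rest of the first postoperative month.

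The boundary also moves with the appointment. A complication on day 12 is acute if the visit is on day 14 and chronic if it is on day 10.

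Toxicity is a named secondary variable (2.5 B), and safety is one of the considerations for planning phase III (2.1). A table laid out by these classes would show mid-postoperative events as chronic toxicity. It would also blend treatment-phase events with surgical ones. About 30% of patients are not operated on (2.3.8), and their acute class contains no surgery, so the class covers different things in different patients within one arm.

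**Working it through.** The plan gives no figure to reproduce here. The check puts the windows on one time axis.

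**Inputs.** Let v be the day of the final visit after surgery: about 10 to 14 (2.3.7). Reporting limit: day 30 after surgery (2.5 D). Postoperative window: day 0 to day 30 (2.5 E).

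**Step 1, operated patients.** Overlap of acute with postoperative morbidity = v. Reported chronic window = 30 − v.

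| Final visit | Acute class inside postoperative window | Reported chronic window |
|---|---|---|
| Day 10 | 10 days (10/30 = 33%) | 30 − 10 = 20 days (67%) |
| Day 14 | 14 days (14/30 = 47%) | 30 − 14 = 16 days (53%) |

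The two parts fill the 30 days. Every reported event in the month after surgery therefore falls in one of the two adverse-event classes and also meets the definition in 2.5 E. No text shown makes the categories exclusive.

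**Step 2, length of the acute class.** Assume surgery 12–16 weeks after randomization, taken from the stated duration of statin therapy. The class then lasts from 12 × 7 + 10 = 94 days to 16 × 7 + 14 = 126 days. The postoperative share of that time runs from 10/122 = 8% to 14/98 = 14%. This is a share of time, not of events.

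**Step 3, inoperable patients.** The acute class ends on the day of the inoperability decision. There is no surgery date, so a limit of 30 days after surgery cannot be applied. Their later events have no usable reporting end date in 2.5 D.

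**Step 4, the two reporting limits.** If the study period in 2.3.10 ends at the final visit, no chronic event would be reported, which contradicts 2.5 D. If it ends later, 2.3.10 does not say when.

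**Step 5, illustration of blending (assumed rates only).** Take 158 per arm, a two-sided 0.05 test, and a composite of any grade 3 or higher acute event. Let p be the presurgical rate and q the early complication rate among operated patients. Take 70% operated (2.4), with toxicity and complications independent. Pooled rate = 1 − (1 − p)(1 − 0.7q), with p assumed to be 15% vs 25%.

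- No pooling: 15% vs 25%, power about 0.60.
- q = 10%: 1 − 0.85 × 0.93 = 21.0% vs 1 − 0.75 × 0.93 = 30.3%, power about 0.47.
- q = 20%: 1 − 0.85 × 0.86 = 26.9% vs 1 − 0.75 × 0.86 = 35.5%, power about 0.38.
- q = 40%: 1 − 0.85 × 0.72 = 38.8% vs 1 − 0.75 × 0.72 = 46.0%, power about 0.25.

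With p = 20% in both arms but 70% vs 80% operated, the pooled rates differ through surgery alone:

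- q = 20%: 31.2% vs 32.8%, a difference of 1.6 points.
- q = 40%: 42.4% vs 45.6%, a difference of 3.2 points.

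**The case against.** The strongest reply is that the stated objective is an all-cause comparison of adverse events, and that the acute and chronic labels do not enter it. An event on postoperative day 12 is reported under either label, and the label does not depend on the arm. No test of either class between arms is specified. Definitions and reporting details are also referred to Appendix 2, which is not shown. This stands in part. It limits the harm to how the safety data are presented and read, but the article itself fixes these windows, so this is not a detail merely left for later.

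Three stronger readings are tempting, and the documents do not support them.

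- *Surgical complications are counted twice.* An event may appear in two separately reported outcomes. Nothing says that the two are added together.
- *Drug toxicity is contaminated.* The plan reports events regardless of cause, so including surgical events in the overall total is legitimate. The weakness is that no phase can be seen separately.
- *The trial loses a known amount of power for safety.* Step 5 needs a composite endpoint that the protocol does not define, and assumed event rates. In tables by CTCAE term, a surgical complication would not dilute a difference in another term.

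It would also be wrong to say that chronic events are defined as ending on day 30. They are recorded without a stated end; only reporting stops.

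A further objection concerns the remedy. Rosuvastatin stops one day before surgery (2.3.7). If each event were allowed in only one window, the treatment-phase class would have no follow-up after the last dose, and the all-cause total would lose its perioperative events. That objection is sound, and the fix below avoids it.

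**Conclusion.** The point holds as a defect in the safety definitions. For operated patients, sections 2.5 D and 2.3.7 together place the cut at about day 10–14 after surgery. The acute class blends treatment-phase events with early surgical complications. The reported chronic class is 16–20 postoperative days and cannot describe chronic toxicity. Both overlap the outcome in 2.5 E. For inoperable patients the reporting limit is undefined, and 2.3.10 and 2.5 D do not clearly agree.

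These conclusions rest only on the stated windows and on subtraction. The size of any dilution or surgery-driven difference between arms cannot be derived from the documents; the figures in step 5 show direction under assumed rates. The pCR endpoint and the sample size are not affected. The change is worth making because it is cheap and alters what the safety comparison shows.

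**What to change.** In section 2.5 D–E:

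1. Keep the all-cause adverse-event total.
2. Compare adverse events between arms by phase, split at the recorded surgery date. The first phase runs from randomization to the day before surgery, or to the end of study in patients not operated on. The second runs from day 0 to day 30 after surgery in operated patients.
3. State that postoperative events appear both in the all-cause total and in postoperative morbidity, and that the two are not summed.
4. Give an explicit reporting end date for patients not operated on, and reconcile 2.3.10 with 2.5 D.
5. Drop the acute and chronic labels, or define them by a fixed time from the end of NACTRT.

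The cost is wording, table programming and some extra tables. It needs no new visit or test. One drawback remains: a late treatment-related event may fall in the postoperative phase. The retained all-cause total covers this.

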#### Assessment of response

2.3.6

Clinical and radiological assessment will be done at 6–8 weeks after completion of NACTRT. Eligible patients will undergo standard surgery (anterior resection, abdominoperineal resection, inter-sphincteric resection, or multi-visceral resection) according to the level and extent of growth. If the reassessment MRI at 12–14 weeks after completion of NACTRT shows inoperable disease, then the patient will be deemed a non-responder and analyzed as part of the non-pCR group. These patients, if on the rosuvastatin arm, will stop the statin on the day they are deemed inoperable by the MDTB. These patients will receive further chemotherapy to downstage the disease as per the current standard of care. A histopathological examination will be conducted for the patients operated on and the pathological response rate and tumor regression grade (TRG) will be judged according to the American Joint Committee on Cancer (AJCC) (**Appendix 1** in **Supplementary Material**). A pCR is defined as no residual cancer found on histological examination of the TME specimen (Grade 0 AJCC or Grade 1 Mandard’s). The pathologist assessing the specimen will be blinded to the treatment that the patient received.

Following surgery and the availability of the histopathology report, the patient would have completed the active phase of the study and will be followed up according to standard follow-up protocol. Survival details will be collected at each follow-up visit or telephonically if the patient misses a visit for any reason.

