### Sample size and duration of the study

2.4

Each year, approximately 180–200 rectal cancer patients receive NACTRT at our hospital, with approximately 70% undergoing surgery and 15%–20% developing progressive disease. The current pCR rate at our hospital following NACTRT is approximately 15%, while the literature indicates a pCR rate of 25%–30% with statin therapy. We hypothesize that rosuvastatin can increase the pCR rate by 10%, from 15% to 25%. To detect a 10% difference in pCR rates, with a two-sided alpha of 0.10 and 80% power, a sample size of 288 patients would be required. Factoring in a 10% attrition rate, the total sample size increases to 316. Approximately 500–600 patients will need to be screened to enroll 316 participants. It is estimated that accrual and analysis will take approximately 3 years to complete.

A follow-on phase III trial is also will be planned depending on the success of the phase II study, which will compare the 3-year DFS in the two arms. All the patients in the phase II study will be included in the survival statistics in the follow-on phase III study which will be statistically powered for survival. Assuming that the addition of rosuvastatin to NACTRT will improve the 3-year DFS from 60% to 67%, our calculated sample size will be 1,135 subjects (567 in the control group and 568 in the treatment group) (a two-sided log-rank test with 80.0% power at a 0.050 significance level). This assumes a uniform accrual pattern across time periods and 10% dropout rate. If we move on to the phase III study, another 4 years will be required for accrual. The total duration will be 7 years for accrual and 3 years for follow up.

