### Statistical analysis

2.6

Quantitative data will be presented as mean ± SD and categorical variables as frequencies within each cohort. The comparison of the statin and non-statin groups will be done using Fisher’s exact test or a χ2 test for categorical variables, and a Wilcoxon rank sum test for quantitative variables. Univariate analysis of significant predictors of an AJCC grade 0 response to NACTRT will be performed by a χ2 or Fisher’s exact test for categorical variables and logistic regression for quantitative variables. Multivariate analysis of statin use as a predictor of AJCC grade 0 responses to NACTRT will be done using multivariable logistic regression models. A Kaplan–Meier survival analysis will be used to determine the effect of statin use and AJCC TRG score on overall survival and disease-free survival. Cox proportional hazard models will be used to determine whether statin use was a significant predictor of recurrence and survival outcomes after adjusting for predicted covariates. All secondary endpoint comparisons will be made using the two-sided log-rank test with a 0.05 significance level. Assuming that OS demonstrates significance in the phase II study, the same criteria would be used for the analysis of PFS. For potential prognostic and predictive factors, multivariate analysis would be performed based on gender, metastasis occurrence from accrual to follow-up timepoint, histology subtype (diffuse, intestinal), and measurable disease (yes, no).

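### DFS and PFS are defined by the same events and neither counts progression, so the planned phase III primary endpoint can miss events or date them late

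*Protocol article*

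**What the plan says.** Section 2.5, item F, sets out DFS as follows: "Disease-free survival is defined as the time from the date of randomization until the date of disease recurrence or until death from any cause". Item G uses the same words for PFS: "Progression-free survival (PFS) is defined as the time from the date of randomization until the date of disease recurrence or until death", where again a death counts whatever its cause. Item G then adds: "Progression will be assessed by the investigator using appropriate workup and investigations, as per routine care". No sentence makes progression an event in either endpoint.

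Section 2.4 describes the hospital's patients on neoadjuvant chemoradiation as "approximately 70% undergoing surgery and 15%–20% developing progressive disease". It sizes phase III on 3-year DFS of 60% versus 67% and includes all phase II patients in that survival analysis.

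A patient found inoperable at reassessment stays in the analysis: section 2.3.6 says "then the patient will be deemed a non-responder and analyzed as part of the non-pCR group", and section 2.3.7 has such patients monitored for survival. Section 2.3.9 describes a different group, patients not operated on despite a response, who are followed for survival and enter the phase III analysis.

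Section 2.6 tests all secondary endpoints by a two-sided log-rank test at 0.05, then says: "Assuming that OS demonstrates significance in the phase II study, the same criteria would be used for the analysis of PFS".

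The status of PFS varies. Table 1A merges it with DFS in one objective, sections 1.3 and 1.4 name DFS only, and section 2.5, item B, lists toxicity and 3-year DFS but not PFS.

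**The concern.** The clock for both endpoints starts at randomization, when every patient has untreated tumour. The event is recurrence, which presupposes that the patient was first made free of disease. Someone whose cancer progresses during or after chemoradiation and who is never resected does not fit that event. Under the printed wording, that patient counts as disease-free until death.

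DFS is secondary in phase II but is the planned primary endpoint of phase III. Patients with growing cancer who count as disease-free inflate the DFS estimate in both arms. Progression before surgery also falls in the period when rosuvastatin is given, so an effect there would show only later, through deaths. If the rule is left open, whether progression counts would be settled in an open-label trial after phase II data exist.

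The testing rule adds an inconsistency: the same variable is tested freely under one name and only after a significant OS result under the other.

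**Working it through.** **1. The definitions side by side**

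| | DFS (item F) | PFS (item G) |
|---|---|---|
| Start | randomization | randomization |
| Events | recurrence; death from any cause | recurrence; death from any cause |
| Progression an event? | no | no, though its assessment is described |
| Test in section 2.6 | log-rank at 0.05, no condition | conditional on significant OS |

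The start and event set are identical, so the two are one variable.

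**2. The plan's phase III figure**

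Inputs from section 2.4: 3-year DFS 60% and 67%, two-sided 0.05, 80% power, uniform accrual, 10% dropout, 7 years' accrual (3 + 4) and 3 years' follow-up, total 1,135.

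- Hazard ratio under exponential survival: ln(0.67)/ln(0.60) = 0.784.
- Events (Schoenfeld): 4 × (1.960 + 0.842)² / (ln 0.784)² ≈ 531. Freedman's formula gives 536.
- With 7 + 3 years and dropout of 10% per year, the mean event probability is 0.462 and the total is 1,149.
- With 4 + 3 years, the event probability is 0.523, giving 1,016; divided by 0.9 this is 1,128.
- With 7 + 3 years and a flat 10% inflation, the total is 972, which does not match.

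The stated 1,135 is thus reproduced within 3% under two plausible readings of accrual and dropout. The target of about 531 events does not depend on which is used.

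**3. How large the unclassified group could be**

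- Phase II: 0.15–0.20 × 316 = 47–63 patients.
- Phase III: 0.15–0.20 × 1,135 = 170–227 patients.
- Share of the assumed control event rate at 3 years (100% − 60% = 40%): 15/40 = 37.5% to 20/40 = 50%.

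**4. Effect on phase III power**

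Assumptions: all of these progressions occur before surgery, all were counted among the 531 planned events, none is picked up as a recurrence, the 15–20% applies to both arms, and the hazard ratio stays at 0.784. The share of progressors dead by the analysis is not given, so a range is shown.

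Events remaining: D = 531 − (170 to 227) × (1 − share dead). Power = Φ(|ln 0.784| × √D / 2 − 1.96).

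| Progressors dead by analysis | Events remaining (15% to 20% progressing) | Power |
|---|---|---|
| none | 361 to 304 | 64% to 56% |
| half | 446 to 418 | 73% to 70% |
| 80% | 497 to 486 | 77% to 76% |
| all | 531 | 80%, with later event times |

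**The case against.** - **Item G may be a drafting slip.** Its text on assessing progression suggests that progression was meant to count in PFS. That is plausible, but a repaired item G would leave item F unchanged, and item F defines the phase III primary endpoint.
- **The whole unresected group should not be treated as unable to recur.** A reader might infer this from section 2.3.8, where about 30% are not operated on. The documents do not support it. Section 2.3.9 recognises patients left unoperated despite a response, and their disease can return. Inoperable patients receive further chemotherapy to downstage the disease (section 2.3.6), so some may later be resected.
- **The loss of 37.5–50% of events is an upper bound.** A reader might take it as the expected loss. The 15–20% is hospital experience rather than a trial estimate, its timing is not stated, and some of these patients may have an event recorded as recurrence. Deaths always count, so many events would be late rather than missing.
- **The OS condition costs little as written.** A reader might infer that a real effect would go untested because OS has the fewest events. But the identical DFS is tested without a condition, so nothing is lost by gating its duplicate. The wording is also loose, although a gate is its plain reading. The condition would matter once PFS had its own definition.
- **Phase III is conditional, and the phase II primary endpoint, pCR, is unaffected.** Both are true. Because phase II patients are pooled into phase III, the event rule should still be settled early.

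These points limit the size of the problem. The identical definitions and the missing progression event remain.

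**Conclusion.** The definitions are wrong as written. DFS and PFS are one variable, and a patient who progresses before being made disease-free has no event until death unless a later recurrence is recorded. This overstates DFS and causes events to be missed or dated late.

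The size depends on facts the article does not give. Under the assumptions listed, phase III power lies between about 56% and 80%, depending mainly on how many progressors have died by the analysis. At 80% the count is preserved but the event times are later. If the 60% control figure was instead derived without counting progression, the power calculation agrees with the printed definition. The endpoint would then still treat progressing patients as disease-free.

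The OS condition on PFS is a secondary inconsistency with little present effect.

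**What to change.** 1. Define the DFS event as the first of disease progression (including before or without surgery), recurrence, or death from any cause, timed from randomization.
2. State how patients who are never resected count, separating progressing or inoperable disease from those not operated on despite a response. Whether a tumour-board decision of inoperability is itself an event is a design choice for the sponsor. It is debatable in an open-label trial because it rests on judgement, and it should be stated either way.
3. Keep one endpoint, or give PFS a definition that differs from DFS, and align Table 1A, sections 1.3 and 1.4, and item B of section 2.5.
4. Remove the OS condition in section 2.6.
5. Confirm that the 60% control 3-year DFS matches the revised definition. If not, restate it and recalculate the 1,135.

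The cost is mainly rewording. The control DFS assumption may become less favourable. Progression would be dated by the investigator under routine care in an open-label trial, and section 2.3.7 plans no protocol-mandated imaging after the active phase, so the dates would depend on routine surveillance. It should be checked that they are recorded in the same way in both arms.
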